### Baseline assessments

Routinely collected ward-level baseline data will be collected for the participating wards (Table 1). In addition, once eligible participants have provided informed consent, individual-level baseline data will be collected either directly from the participant or via trust staff (see Table 1).

**Table 1 Tab1:** Baseline data

**Measure**	**Description**
**Ward-level baseline data:**	
Ward-level readmission rates	Number of patients discharged by participating ward and the total number of 30-day readmissions to any ward in the hospital trust. Collected for the 12-month period of 2019 (prior to the COVID-19 pandemic). Data will be reported on a monthly basis and will be dichotomised by age (< 75 years and ≥75 years).
Average length of stay	Collected for the 12-month period of 2019 (prior to the COVID-19 pandemic). Data will be reported on a monthly basis and will be dichotomised by age (< 75 years and ≥75 years).
Age of patients	Median and mean ages of patients. Data collected for the 12-month period of 2019 (prior to the COVID-19 pandemic) and reported on a monthly basis.
**Individual level baseline data:**	
Patient demographics	Age; gender; ethnicity; first language; living/carer arrangements.
EuroQol 5-Dimension Health Questionnaire (5 levels) (EQ5D-5L) and Proxy EQ5D-5L [37]	A measure of health state (quality of life) comprising five dimensions: mobility, self-care, usual activities, pain/discomfort, and anxiety/depression. Scores can be used to facilitate the calculation of quality-adjusted life years (QALYs).
Functional Co-morbidity Index [41]	A sum of 18 self-reported comorbid conditions with a score of 0 to 18. A higher FCI score indicates greater comorbidity and is associated with impairment in physical function 1 year later,
Admission information	Date of index admission and discharge; type of index admission (planned/unplanned); reason for index admission; number of admissions in previous 12 months.

### Follow-up assessments (see the “ Outcomes” section above)

Following discharge from hospital, we will follow up recruited participants on control and intervention at three time points:Time 1 — post discharge: data collection will occur ideally between 5 and 17 days but up to a maximum of 21 daysTime 2 — 30 days post discharge: data collection will occur ideally between 30 and 45 daysTime 3 — 90 days post discharge: data collection will occur ideally between 90 and 105 days

At the point of recruitment, all participants will be advised that they will receive a questionnaire in the post and may receive a telephone call a few days later (as a reminder, to check receipt of the questionnaire or to offer support to complete). For participants who do not return questionnaires, a reminder will be sent out in the post and following this, one more reminder phone call will be made totalling up to four attempts to contact participants at each follow-up. Where contact is not made this will be recorded as missing data. Subsequent follow-ups will be initiated as planned. Researchers will not contact patients who have died since discharge.

If a patient loses capacity during the trial and therefore cannot complete the outcome measures, recruitment procedures will be followed to identify a personal consultee. Follow-up data will only be collected about participants who have lost capacity if the appropriate consent is in place. Participants will be given an unconditional £5 voucher at each follow-up time point.

### Data management, monitoring and safety reporting

Patient data will be recorded on case report forms (CRFs). Participants will be assigned a unique identification number and all data will be anonymised for analysis and reporting purposes. Electronic data (including qualitative data) and wet ink copies of the CRFs will be stored securely at the York Trials Unit (YTU) or Bradford Institute for Health Research. Data will be monitored for quality and completeness by YTU.

The trial is overseen by the Trial Management Group (TMG) comprising of the chief investigator, key co-applicants, and the operational members of the Yorkshire Quality and Safety Research group (YQSR) and YTU. An independent combined Trial Steering Committee (TSC) and Data Monitoring Committee (DMC) comprising academic, NHS England, clinical, and a patient representative meet bi-annually. Further details are available on request.

In this patient population, as death, falls, pressure ulcers, and medication issues are expected for some, these events will not be subject to expedited reporting to the main Research Ethics Committee (REC), but will be reported annually to the REC (in routine annual progress reports). There is no anticipated harm and compensation for trial participation. Quantitative monthly patient safety incident reports (via Datix) and qualitative contextual data (where required) will be gathered throughout the study. We will compare patient safety incident data in intervention wards against the same month in the previous year. Further contextual data will be sought from ward managers and local principal investigators if trends in data suggest an increase in events during the intervention period. This information will be reviewed regularly at meetings and via emailed reports from the TMG to the PMG and TSC/DMC in accordance with the Trial Monitoring plan.

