### Randomisation

Wards will be randomly allocated in an equal allocation ratio (1:1) with 20 randomised to the Intervention and 20 to care-as-usual. Random allocation will be undertaken independently by the York Trials Unit (YTU) with minimisation using minimPy [29] and stratified by ward type (speciality), the percentage of patients over 75 years (split by ≤66% and >66%, based on the feasibility cRCT) and NHS trust.

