#### Delivery

Ward staff will be asked to deliver the intervention to all patients who are returning back to their own homes irrespective of age for the 4- to 5-month period during which patient recruitment takes place on the ward. This is to ensure that YCNY becomes usual care on the intervention wards. In the trial, however, only those meeting our eligibility criteria (i.e. adults aged 75 years and over and returning to their own or a relative’s home) will be recruited to follow-up. Recruitment will start on completion of the intervention embedding period. Patients who consent to the trial are likely to have been exposed to the intervention, although this will not be a condition of participation.

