## Trial status

This article refers to protocol version 9 dated 5/7/2021. Recruitment began on 8/11/2021 with completion expected by the end of March 2023. Post-discharge data collection is due to finish in May 2023. The study end date is October 2023 to allow for post-discharge data query clarification.

First submitted 19/01/23. Due to a processing error, resubmitted 25/7/23.

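### The stated comparison for ward safety incidents sets intervention wards against the previous year, so year-on-year change can raise a false signal or mask a true increase; concurrent control wards would remove it

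*Protocol article*

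**What the plan says.** The section on data management, monitoring and safety reporting describes the data source: "Quantitative monthly patient safety incident reports (via Datix) and qualitative contextual data (where required) will be gathered throughout the study". It then fixes the comparator: "We will compare patient safety incident data in intervention wards against the same month in the previous year". Ward managers and local principal investigators are asked for more context "if trends in data suggest an increase in events during the intervention period". Oversight follows: "This information will be reviewed regularly at meetings and via emailed reports from the TMG to the PMG and TSC/DMC", under a Trial Monitoring plan that is not shown. The section gives no incident rate, threshold or denominator.

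The Randomisation section allocates 40 wards, "with 20 randomised to the Intervention and 20 to care-as-usual". The article nowhere describes a comparison of incident reports with the control wards. Under Delivery, each ward delivers the intervention "for the 4- to 5-month period during which patient recruitment takes place on the ward". Trial status gives the calendar: "Recruitment began on 8/11/2021 with completion expected by the end of March 2023".

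The Discussion describes conditions that were not stable. Its Contamination part says closures of wards and bays have become more common since the pandemic began, and that more patient movement is possible. Its Implementation part describes added stress on services and staff absence.

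**The concern.** A same-month, previous-year comparison within the intervention wards holds the ward and the season constant. It does not hold the year constant. Anything that changed between the two years enters the contrast together with any effect of YCNY: occupancy, case mix, staffing, or readiness to file a Datix report.

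The two possible errors are handled unequally. An apparent rise leads to a contextual enquiry, where a pandemic explanation can come to light. A background fall that offsets a true increase leaves no apparent rise, so nothing prompts anyone to look.

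The stake is the quality of the ward-level safety information that reaches the TSC/DMC. Expected events such as falls, pressure ulcers and medication issues go to the ethics committee only in annual reports, so the Datix comparison is the main timely ward-level signal that the article describes. A randomised comparison group exists for the same calendar period and is not named for this purpose.

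**Working it through.** The plan gives no figure for safety monitoring, so there is none to reproduce. The check covers the calendar, the algebra of the two contrasts, and an illustration on assumed inputs.

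**Calendar.** Recruitment runs from November 2021 to an expected end in March 2023. The same months one year earlier run from November 2020 to March 2022. Both periods fall after the pandemic began, and the article reports changing ward conditions since then.

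**Algebra.** Let R be the true rate ratio for YCNY and S the background ratio of this year to last year.
- Before-after ratio on intervention wards = R × S.
- Intervention versus concurrent control = (R × S) / S = R, provided the background change is common to both arms.

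**Ratios.** S from 0.8 to 1.3 and R = 1.25 are assumptions.

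| Background S | Before-after, R = 1.00 | Before-after, R = 1.25 |
|---|---|---|
| 0.8 | 0.80 | 1.00 |
| 0.9 | 0.90 | 1.125 |
| 1.0 | 1.00 | 1.25 |
| 1.1 | 1.10 | 1.375 |
| 1.2 | 1.20 | 1.50 |
| 1.3 | 1.30 | 1.625 |

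The concurrent ratio is 1.00 throughout the middle column and 1.25 throughout the last. Full masking needs S = 1/R: for R = 1.25 that is 1/1.25 = 0.80, a 20% fall. A 20% increase with a 20% fall does not cancel exactly: 1.2 × 0.8 = 0.96.

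**Chance of an upward flag.** Further assumptions: 20 wards per side, 5 months, 5 or 10 incidents per ward per month, Poisson counts without clustering, and a flag when log(ratio)/SE exceeds 1.96. That flag is a device for illustration; the plan has no such rule.
- At 5 per ward-month the reference count is 20 × 5 × 5 = 500.
- R = 1, S = 1.2: the current count is 600. SE = sqrt(1/500 + 1/600) = 0.0606 and log 1.2 = 0.182, so z = 3.01. The chance of a flag is 85%, and 99% at 10 per ward-month.
- R = 1, S = 1.1: the chance is 34% at 5 per ward-month and 59% at 10.
- With R = 1 the concurrent contrast flags 2.5% of the time for every S.
- R = 1.25, S = 0.8: the before-after counts are 500 and 500, so the ratio is 1.00 and the chance of a flag is 2.5%. The concurrent counts are 500 and 400. SE = sqrt(1/500 + 1/400) = 0.0671 and log 1.25 = 0.223, so z = 3.33 and the chance is 91% (99.7% at 10 per ward-month).

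These probabilities are optimistic about precision. Overdispersion, differences between wards and staggered ward starts would widen the standard errors. Differences between wards affect the concurrent contrast most, because the before-after contrast uses each ward as its own reference. None of this removes the factor S from the before-after ratio.

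**The case against.** The previous-year comparison is a surveillance screen. No test, threshold, stopping rule or conclusion about harm depends on it. A reader might infer that pandemic-era shifts will be read as harm, but the documents do not support that: an apparent rise leads to contextual enquiry and committee review. This part of the objection stands, and it leaves masking as the stronger half of the point.

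A reader might also infer that this is the trial's only safety comparison. It is not. Patient-reported safety events are collected in the nested cohort, which is followed up in both arms. Deaths within 30, 60 and 90 days come from routine data, and readmissions are compared by arm. The point holds for ward incident reports alone. Those other data concern the period after discharge and do not replace ward incident monitoring.

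It is also tempting to say that control-ward reports are not gathered, or that no denominator will be used. The article does not restrict the Datix reports to one arm, and the Trial Monitoring plan may settle both matters. Silence here proves neither. What remains is that the comparison the article does state is historical and within one arm.

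Nor does the use of 2019 for ward-level baseline data show an inconsistency. Those figures describe wards at baseline, which is a different purpose. A 2019 safety comparator would set pandemic-era months against pre-pandemic ones, so the previous year has some rationale.

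Finally, concurrent controls remove common background change, not every bias. Ward staff are not blinded, and YCNY could alter how readily incidents are reported.

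**Conclusion.** The point holds as a weakness of the stated monitoring comparison. The before-after ratio equals the true effect multiplied by year-on-year change, and the article itself gives reasons to expect such change. With no true effect, assumed shifts of -20% to +30% give ratios of 0.80 to 1.30 where the concurrent ratio is 1.00. A true 25% increase with a 20% background fall gives 1.00 where the concurrent ratio is 1.25, and no enquiry follows.

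The incident rates, the shifts and the flag rule are all assumptions. The structural result needs only that background change is shared by the two arms. The documents do not show that any shift occurred, or in which direction, so background change can mislead; it cannot be said that it will. The change is worth making, but the primary outcome and the effectiveness analyses do not depend on it.

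**What to change.** - Obtain the same monthly Datix counts for the control wards over the same calendar months, if they are not already gathered.
- Express them as rates, with occupied bed-days or discharges as denominator, since closures change the number of patients at risk.
- Make intervention versus concurrent control the monitoring comparison reported to the TSC/DMC.
- Keep the previous-year figures for both arms as baseline context, so that the change can be compared between arms. This also takes account of stable differences between wards.
- State this in the Trial Monitoring plan, or, if that plan already provides for it, say so where the article describes the comparison.

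The cost is routine extracts from up to 20 more wards and a revised monitoring plan, with no patient contact. Differential reporting by unblinded staff would remain and should be noted when the rates are read.

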### Statistical analysis

A CONSORT diagram will document the flow of wards and participants through each stage of the trial.

Readmission rates will be summarised descriptively at each time-point by treatment group and overall. The primary analysis will use a repeated-measures mixed model to compare the treatment groups. This will account for the hierarchical nature of the data by including Trust and ward as random effects and the repeated measurements from participants will be modelled by the covariance structure. The outcome will be readmission (yes/no) at 30, 60 and 90 days and the model will include important baseline covariates (e.g. minimisation factors), treatment group and time as fixed effects. An interaction term assessing whether the difference between the treatment groups changes over time will also be included in the model.

The primary analysis will compare the groups at 30 days. Secondary analyses will compare the two groups at 60 and 90 days post-discharge

Detailed statistical methods will be outlined in a separate Statistical Analysis Plan.

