**Methods:**

A multi-centre cluster randomised controlled trial (cRCT) will evaluate the effectiveness and cost-effectiveness of the YCNY intervention.

Forty acute hospital wards (clusters) in England from varying medical specialities will be randomised to deliver YCNY or care-as-usual on a 1:1 basis. The primary outcome will be unplanned hospital readmission rates within 30 days of discharge. This will be extracted from routinely collected data of at least 5440 patients (aged 75 years and older) discharged to their own homes during the 4- to 5-month YCNY intervention period. A nested cohort of up to 1000 patients will be recruited to the study to collect secondary outcomes via follow-up questionnaires at 5-, 30- and 90-day post-discharge. These will include measures of patient experience of transitions, patient-reported safety events, quality of life and healthcare resource use. Unplanned hospital readmission rates at 60 and 90 days of discharge will be collected from routine data.

A process evaluation (primarily interviews and observations with patients, carers and staff) will be conducted to understand the implementation of the intervention and the contextual factors that shape this, as well as the intervention’s underlying mechanisms of action. Fidelity of intervention delivery will also be assessed across all intervention wards.

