### Outcomes

The *primary outcome measure* (*N*=5440) is unplanned hospital readmission rates at 30 days post-discharge. It will be assessed using routine data recording the dates of all unplanned hospital readmissions up to 30 days post-discharge from the participant’s index admission.

*Secondary outcome measures* are listed below with further details available in Supplementary file 1:Patient At Care Transitions Measure (PACT–M) [30]Care Transitions Measure 3 items (CTM-3) [35]Questions regarding post-hospital syndrome [36]EuroQol 5-Dimension Health Questionnaire (5 levels) (EQ5D-5L) and Proxy EQ5D-5L [37]Healthcare Resource Use [38]Questions regarding exposure to and utility of the interventionUnplanned hospital readmissions at 60 and 90 days.

Permission to obtain unplanned hospital readmissions data from non-individually consented patients was provided through the United Kingdom Confidentiality Advisory Group (21/CAG/005). Patients will be able to opt out of this process through the provision of an information leaflet on the wards that details the contact details for the research team.

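### The primary 30-day comparison is taken from a three-time-point model of nested readmission indicators, which adds nothing at 30 days and makes the result depend on an unnamed covariance choice

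*Protocol article*

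**What the plan says.** The Statistical analysis section fixes the model class: "The primary analysis will use a repeated-measures mixed model to compare the treatment groups". Its dependent variable has three values per patient: "The outcome will be readmission (yes/no) at 30, 60 and 90 days". Clustering enters by "including Trust and ward as random effects", and for the patient level "the repeated measurements from participants will be modelled by the covariance structure". Treatment, time, their interaction and baseline covariates such as the minimisation factors are fixed effects. The 30-day contrast is primary; 60 and 90 days are secondary. Link function and covariance structure are not named, and detail is left to a separate SAP.

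The outcome is defined elsewhere. In the Abstract: "The primary outcome will be unplanned hospital readmission rates within 30 days of discharge", and "Unplanned hospital readmission rates at 60 and 90 days of discharge will be collected from routine data". In Outcomes, the primary measure uses "routine data recording the dates of all unplanned hospital readmissions up to 30 days post-discharge". Under Other data collected, the time to each unplanned readmission is also obtained. The Discussion (Recruitment and follow-up) expects no particular difficulty in getting the routine readmission data.

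**The concern.** On the natural reading, readmission by 30, 60 and 90 days are nested events. Only four of the eight possible yes/no patterns can occur: 111, 011, 001 and 000. These are not three measurements of one quantity that varies within a person.

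A repeated-measures model earns its place when later or earlier values help to recover missing data at the primary time point. Here they cannot. A dated record that gives a patient's status at 60 or 90 days also gives it at 30 days. The later rows therefore bring no gain to the primary contrast, but they do make it depend on how within-patient dependence is modelled, on one ward effect serving all three times, and on covariate effects being constant over time. At stake are the standard error and power of the primary test and, under one way of fitting the model, the scale of the estimate itself.

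**Working it through.** **1. Inputs.** From Patient population and sample size: control risk 18%, reduction 4.5 points (so 13.5%), 80% power, alpha 0.05 (taken as two-sided), ICC 0.01, cluster size 140, attrition 10%, N = 5440. From Randomisation: 20 + 20 wards. The article gives no 60- or 90-day rates. Assumed control values are 24–27% at 60 days and 28–33% at 90 days, with 25% and 30% as the central case.

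**2. The plan's own figure.** Per arm, n = (1.960 + 0.842)² × (0.18×0.82 + 0.135×0.865) / 0.045² ≈ 1,025. Design effect = 1 + 139 × 0.01 = 2.39. Total = 2 × 1,024.7 × 2.39 / 0.9 = 5,442, against 5,440 stated. (With the pooled variance under the null, 1,028 per arm gives 5,460.) The stated size is thus a single-time-point 30-day calculation that takes no credit for repeated measures.

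**3. Forced correlation.** For nested events, corr(Y_s, Y_t) = √[p_s(1−p_t) / (p_t(1−p_s))]. At 18%, 25% and 30%:
- 30 with 60 days: √(0.135/0.205) = 0.81
- 30 with 90 days: √(0.126/0.246) = 0.72
- 60 with 90 days: √(0.175/0.225) = 0.88

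**4. Best case: no change.** A marginal (GEE) logistic model with arm, time and arm × time was fitted to one simulated complete data set, without covariates or ward terms. It gave a 30-day log odds ratio of −0.23424 (SE 0.07401), under both exchangeable and independence structures. The 30-day rows alone gave the same two numbers.

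**5. Linear model, one common variance, one shared ward effect.**
- *Simplified calculation.* Variances at the three times are 0.1476, 0.1875 and 0.2100, mean 0.1817, and √(0.1817/0.1476) = 1.11. With 4,896 analysed (2,448 per arm, 122.4 per ward), the design effect is 1 + 121.4 × 0.01 = 2.214 and SE = √(0.2644 × 2.214 / 2448) = 0.01546. Then z = 0.045/0.01546 = 2.91 and power is 82.9%. With the SE multiplied by 1.11, power is 74.6%.
- *Simulation.* 1,500 runs per scenario, 40 wards × 136 patients, ICC 0.01. The 30-day point estimate was unbiased throughout.

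| Ward effects after day 30 | Assumed control 60/90-day rates | Mean SE, joint model | Mean SE, 30 days only | Ratio | Power, joint vs 30 days only |
|---|---|---|---|---|---|
| Persist | 27% / 33% | 0.01978 | 0.01494 | 1.32 | 63.5% vs 83.5% |
| Persist | 24% / 28% | 0.01846 | 0.01504 | 1.23 | 69.3% vs 83.4% |
| Do not persist | 27% / 33% | 0.01532 | 0.01500 | 1.02 | 82.4% vs 83.6% |
| Do not persist | 24% / 28% | 0.01522 | 0.01497 | 1.02 | 83.3% vs 83.5% |

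Under no treatment effect with persisting ward effects, the joint model rejected in 1% to 2% of runs. The error is therefore conservative.

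**6. Logistic model with a participant random intercept.** Expected pattern frequencies (111, 011, 001, 000) were 0.18/0.07/0.05/0.70 in control and 0.135/0.07/0.05/0.745 in intervention. The marginal 30-day odds ratio is (0.135/0.865)/(0.18/0.82) = 0.71.

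| Participant SD | Minus log-likelihood (two arms summed) | 30-day odds ratio |
|---|---|---|
| 0 | 3.115 | 0.71 |
| 4 | 1.916 | 0.42 |
| 8 | 1.778 | 0.21 |

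The fit keeps improving as the SD grows. With the 27%/33% rates, −2 log-likelihood at SD 32 is 3.717 against 3.716 for the saturated model. There is no finite maximum, so the reported odds ratio would reflect where the software stopped.

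**The case against.** The strongest reply is that the worst figures belong to models the article does not describe. It names only Trust and ward as random effects and assigns patient dependence to a covariance structure, which reads as marginal modelling. The drift in the odds ratio needs a participant random intercept that is nowhere specified. A reader might infer from step 6 that the planned primary estimate is biased; the text does not support that.

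The standard-error inflation, in turn, needs an identity-scale model with a common variance. A logistic model uses p(1−p) at each time. An approximate check at the assumed 18/25/30% rates found that sharing a persistent ward effect inflated the SE by about 18% on the identity scale but only about 2% on the logit scale. Link and covariance may be settled in the SAP, which is not shown.

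A reader might also infer that the treatment-by-time interaction is meaningless. It is not: whether the difference in cumulative readmission changes between 30, 60 and 90 days is a legitimate question, and correlation between the times is what a covariance structure is for.

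All of this stands and limits the severity. It does not restore any benefit. The three-row primary model is stated in the article itself, and its best outcome is the answer that the 30-day data give alone.

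**Conclusion.** The point holds as an avoidable weakness in the primary model, not as a demonstrated error in its result. The later rows add nothing at 30 days. Depending on choices the article leaves open, the 30-day standard error is unchanged, about 2% larger, or up to about 30% larger. In the last case power falls from about 83% to about 64–69%, with type I error below nominal. The odds-ratio drift arises only under a participant random intercept.

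This rests on three assumptions:
- The 60- and 90-day indicators are cumulative from discharge. This is the natural reading, but the Statistical analysis section does not say so; with separate 30-day windows the nesting argument would fail.
- 30-day status is near complete. The Discussion supports this, although the sample size allows 10% attrition.
- The 60- and 90-day rates are assumed, as is the extent to which ward effects persist.

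The exact equality in step 4 was checked without covariates or ward terms. The sample size is not called into question.

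**What to change.** Make the primary analysis a mixed-effects logistic model of 30-day readmission: one row per index discharge, random effects for ward and Trust, and treatment and the minimisation factors as fixed effects. Fit the same model separately at 60 and 90 days for the secondary comparisons, and state that these outcomes are cumulative from discharge. Any analysis of change over time, for example time to first readmission from the times already collected, should be labelled secondary or exploratory. Contrasts restricted to patients not yet readmitted condition on a post-randomisation event and should not be presented as randomised comparisons.

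The cost is a change of wording in the protocol and SAP. It needs no new data, loses no precision at 30 days and leaves the sample size as it is. It should be made before the comparative data are seen. The article, published in the month of the planned study end, does not say whether that is still possible; if it is not, the 30-day model should be reported beside the planned one and the change dated.
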